### Hypotheses

The following detailed study hypotheses for the main outcome (i.e., reduction in the monthly days of cannabis use between baseline and the 3- and 6-month follow-up assessments) will be tested:A mindfulness-based self-help IMI for the reduction of cannabis use (study arm 1) is more effective than being on a waiting list (control condition, study arm 3).A CBT-based self-help IMI for the reduction of cannabis use (study arm 2) is more effective than being on a waiting list (control condition, study arm 3).A mindfulness-based self-help IMI for the reduction of cannabis use (study arm 1) is at least as effective as a CBT-based self-help IMI (study arm 2).

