
**Table 3 Tab3:** Overview of all measures and their measurement time points

	**Assessment instruments**	**Base-line (t**_**0**_**)**	**6 weeks (t**_**1**_**)**	**3 months follow-up (t**_**2**_**)**	**6 months follow-up (t**_**3**_**)**
1	Socio-demographics (age, gender, sexual orientation, educational attainment, migration background, financial situation)	X			
2	Cannabis Use Disorders Identification Test (CUDIT-R)	X	X	X	X
3	*Cannabis use*				
3a	Consumption Patterns (Years of Use, 30-day point prevalence of cannabis and CBD abstinence, Type of Consumption)	X	X	X	X
3b	Defining the personal standard joint	X			
3c	TLFB (Cannabis use frequency and amount for the last 7 days in standard joint units)	X	X	X	X
4	Severity of Dependence Scale (SDS)	X	X	X	X
5	Short version of the Alcohol Use Disorders Identification Test (AUDIT-C)	X		X	X
6	National Institute on Drug Abuse *Screening (NIDA ASSIST)*	X		X	X
7	Drug Abuse Screening Test (DAST-10)	X			
8	Perceived Stress Scale (PSS-10)	X	X	X	X
9	Patient Health Questionnaire for Depression (PHQ-9)	X		X	X
10	Generalized Anxiety Disorder Screener (GAD-7)	X		X	X
11	Adult ADHD Self-Report Scale (ASRS-V1.1)	X			
12	Mindfulness Attention Awareness Scale (MAAS)	X	X	X	X
13	Comprehensive Inventory of Mindfulness Experiences (CHIME)	X			
14	Previous experience in meditation (no official instrument)	X			
15	Client Satisfaction Questionnaire for Internet Interventions (CSQ-I)		X^a^		
16	Negative effects, according to Rozental et al. (2015)		X		
17	Use of any services besides CANreduce			X	X
18	Adherence and Retention^b^		X		

^a^ Only for study arms 1 and 2

^b^ Adherence and retention are constructs measured indirectly and not part of a questionnaire

The primary study outcome is the number of days of cannabis use over the preceding 30 days.

Secondary outcomes are quantity and frequency of cannabis use over the last seven days’; scores for the SDS, AUDIT-C, NIDA-ASSIST, PSS-10, PHQ-9, GAD-7, MAAS, and CSQ-I., and any negative effects attributed to the program.

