### Data analyses

Data will be analyzed according to the ITT principle. Multiple imputation procedures, using the R package *mice* [87], will be used to address missing data. *mice* involves specifying a multivariate distribution for the missing data and drawing imputations from their conditional distributions by Markov chain Monte Carlo (MCMC) techniques. We intend to use 20 imputed data sets, as this has been deemed sufficient [87]. The imputation model will include all primary and secondary outcomes (see above). Adjunct variables, like sociodemographic data, will be included if they improve convergence within the imputation model.

Differences in primary and secondary continuous outcome variables between the two active study arms (1 and 2) at baseline and at both follow-up points will be tested using linear mixed models (LMM). The LMMs will be specified to model clusters and repeated measures by defining random effects for study condition and time (repeated measures). Appropriate distributions for non-normal continuous outcomes will be specified (e.g., negative binomial, zero-inflated). In addition to the ITT analyses, per-protocol analyses will be performed.

To investigate the exploratory research question of whether study arm 1 (mindfulness-based self-help IMI) results in a similar reduction in days of cannabis use as study arm 2 (CBT-based self-help IMI), a confidence interval approach will be used for the ES of the difference between these two study arms, using a two-sided 0.05 level of significance [54]. The equivalence margin is a priori set at d = 0.20, corresponding to the smallest value that would constitute a relevant effect [88]. The upper bound of the 95% CI for the ES will be compared against the predefined equivalence margin of d = 0.20 and must be below the margin to show equivalence.

Additional exploratory regression analyses will be conducted to determine whether baseline variables predict the frequency or quantity of cannabis use, severity of dependence (SDS), reduced psychiatric symptoms (PHQ-9, GAD-7), perceived stress (PSS-10) and mindfulness (MAAS) at 3 and/or 6 months follow-up, treatment retention, and adherence. For these analyses, we will use linear, multinomial, or binary regression models, depending on the scale used for the outcome measure. Treatment retention and client satisfaction will be compared between study arms one and two by Pearson chi-square analysis at week 6 (intervention end).

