### Power analysis

Following best-practice procedures for LMM, power analysis was based on a Monte Carlo simulation. Based on pre-specified LMM model parameters, new values for the primary outcome were simulated and tested by z-tests for the comparison between study arms 1 and 3 (main hypothesis). This procedure was iterated 1000 times using simulated replicates. Power resulted from the number of significant effects identified across simulations (see [89]). The model parameters were derived from the CANreduce 2.0-RCT [19], due to its similar study design and measurements. We estimated a two-level Poisson generalized linear mixed model (GLMM) with random slopes and fixed effects for "measurement time", "study condition", and "condition*time". The CANreduce 2.0 model estimate yielded an effect of b = -0.069 (*p* = 0.07) for the interaction. This value was reduced to -0.06 for the power analyses to account for the smaller ES that have been established in meta-analyses [10]. The simulation indicated a power > 80% for *n* = 210 per study arm. Hence, a total sample of 630 frequent cannabis users will be targeted.

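### Neither 3 nor 6 months is primary and no success rule is set for arm 1 versus arm 3, while the >80% power is for one condition-by-time effect and not for a test at a single follow-up

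*Protocol article*

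**What the plan says.** Four places in the protocol article bear on this.

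- **Measures:** "The primary study outcome is the number of days of cannabis use over the preceding 30 days". No assessment time is attached.
- **Hypotheses:** the main outcome is the "reduction in the monthly days of cannabis use between baseline and the 3- and 6-month follow-up assessments", and three hypotheses on it are to be tested. Two follow-ups therefore sit inside one main outcome.
- **Data analyses:** differences are examined "at baseline and at both follow-up points will be tested using linear mixed models (LMM". That sentence names only arms 1 and 2. The section gives no primary follow-up, order or adjustment, and names no test for arm 1 versus arm 3.
- **Power analysis:** simulated outcomes were "tested by z-tests for the comparison between study arms 1 and 3 (main hypothesis". The model is described as follows: "We estimated a two-level Poisson generalized linear mixed model (GLMM) with random slopes and fixed effects" for time, condition and their interaction. One interaction coefficient carries the effect.

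The Design section makes arm 1 the arm of primary interest. Arm 2 is a reference, and its comparison with control helps judge whether the trial was sensitive. So the comparisons are ranked, but the follow-ups are not.

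**The concern.** The wording fits three success rules for arm 1 versus arm 3: a win at either follow-up, a win at both, or one joint effect across time. They differ in false-positive risk and in power, and only the joint effect corresponds to what was simulated. The choice should be fixed before anyone sees outcomes by arm. That matters more here because the article says study personnel are not blinded and that data will be extracted at several time points.

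A smaller, related matter is baseline. The questionnaire is completed before randomisation, so any difference at baseline between randomised arms is chance, and a significance test of it answers no question. A model that leaves the arms free to differ at baseline makes the treatment comparison one of change from baseline, which uses the baseline value less efficiently than adjusting for it.

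**Working it through.** **1. The stated power.** Inputs from the Power analysis section: "model estimate yielded an effect of b = -0.069" with p = 0.07; "This value was reduced to -0.06 for the power analyses"; n = 210 per arm; power above 80%. The simulation cannot be rebuilt, because the variances, baseline rate, time coding and size of the earlier trial are not given. A rough Wald check, assuming two-sided p-values, is possible:

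- SE in the earlier trial: 0.069 / 1.812 = 0.0381.
- SE needed for 80% power at 0.06: 0.06 / (1.960 + 0.842) = 0.0214.
- Variance ratio: (0.0381 / 0.0214)² ≈ 3.16. So 210 per arm gives 80% if the earlier estimate rested on about 210 / 3.16 ≈ 66 per arm.
- If it rested on 50, 66, 80 or 100 per arm (assumed), power at 210 is 90%, 80%, 72% or 63%.

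The >80% is therefore neither confirmed nor refuted.

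**2. Type I error for arm 1 versus arm 3 under each rule.** Two-sided 5% per test is assumed; the article states that level only for the interval comparing arms 1 and 2. The correlation ρ between the 3- and 6-month test statistics is not given, so it is varied (1,000,000 simulated pairs).

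- Win at either time, independent tests: 1 − 0.95² = 9.75%, the ceiling for non-negative ρ.
- Win at either time, correlated tests: 9.1% (ρ = 0.5), 8.3% (0.7), 7.8% (0.8), 7.0% (0.9).
- Win required at both: at most 5%.
- One condition-by-time test: 5%.

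**3. Power at a single follow-up.** Take a linear trend on the log scale with slope variance 1 and residual variance k, and scale it so that the slope test has exactly 80% power at n = 210. The slope estimate has variance proportional to 1 + k/Sxx, where Sxx is the sum of squared deviations of the time codes. Change from baseline at time t, per unit of slope, has variance proportional to (t² + 2k)/t². Power at t is Φ(2.802 × √[(1 + k/Sxx) / ((t² + 2k)/t²)] − 1.960).

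Worked case with codes 0, 1, 2 and k = 1, so Sxx = 2:

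- Slope variance: 1 + 1/2 = 1.5.
- 6 months (t = 2): (4 + 2)/4 = 1.5, so power is 80%.
- 3 months (t = 1): 1 + 2 = 3, so power is Φ(2.802 × √0.5 − 1.960) = Φ(0.02) ≈ 51%.

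Over four time codings (0-1-2-3, 0-1-2, and months with and without the 6-week visit) and k from 0.25 to 64:

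| Rule | Power |
|---|---|
| 3 months alone | 29-78% |
| 6 months alone | 76-80% |
| Both required | 28-77% |
| Either, unadjusted | 79-83% |
| Either, 2.5% each | 70-74% |

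In these scenarios ρ runs from 0.51 to 0.98, and the either-time error from 9.0% down to 5.9%. Apart from this model, if each follow-up had 80% power, requiring both would give 64% (ρ = 0) to 75% (ρ = 0.9).

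**4. Baseline.** For a simple linear comparison with one baseline and one follow-up of equal variance and correlation r, the variance after adjustment relative to change scores is (1 − r²) / [2(1 − r)] = (1 + r)/2. That is 0.75 at r = 0.5 and 0.85 at r = 0.7. The article gives no r, and its power model is a Poisson mixed model with random slopes, so these values only illustrate the direction.

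**The case against.** The strongest defence is that the only test described for the main hypothesis is the z-test on the condition-by-time term. If that is what will be run, its level is 5% and the power statement matches it. The Hypotheses section joins the two follow-ups with an and, which does not read as a licence to claim success at either. The sentence about testing at baseline and at each follow-up concerns arms 1 and 2, not arm 1 versus arm 3. A statistical analysis plan that is not shown may settle the rest.

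Much of this stands, and it rules out several stronger conclusions that a reader might draw:

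- **That type I error is inflated.** It is inflated only under the either-time rule, which the text permits but does not state.
- **That the risk is 15-16%.** This counts a lone win for arm 2 versus arm 3 as trial success. The Design and Power analysis sections rank arm 1 versus arm 3 first, so arm 2 is not co-primary.
- **That the power belongs to a different test.** It would match a condition-by-time test. What is missing is a statement that this is the test.
- **That linear mixed models contradict the Poisson power model.** The abstract and the Data analyses section both allow generalized models and suitable distributions.

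The defence does not close the gap. A power section describes a simulation, and the Data analyses section does not adopt that test for arm 1 versus arm 3. The time point is part of the definition of the primary outcome. The article states that outcome itself, once with two times and once with none, so this is not detail that can be left to a later plan.

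**Conclusion.** The point holds in a limited form. For arm 1 versus arm 3 the article fixes neither a primary follow-up nor a rule for combining two. The consequence depends on the rule chosen later:

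- **Either time:** about 7-10% type I error over correlations from 0.9 down to 0.
- **Both times:** error controlled, power reduced.
- **One joint effect:** both properties as stated, subject to the unverified >80%.

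The >80% is not shown for a single follow-up, and the shortfall is likely to be greatest at 3 months. These figures rest on two-sided 5% tests and assumed correlations; the power ranges also rest on a linear trend and assumed time codings and variance ratios.

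The baseline matter is secondary. The significance test of arms 1 and 2 at baseline serves no hypothesis, and the gain from using baseline better cannot be sized without the baseline-to-follow-up correlation.

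**What to change.** Before outcome data are analysed, state in the analysis plan and registry:

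1. **One primary test for arm 1 versus arm 3.** Use either the condition-by-time effect that was powered, with its time coding and the visits that enter it, or the contrast at one named follow-up. In the second case, test the other follow-up next at 5%, and only if the first succeeds.
2. **Power for that test**, rerun at 210 per arm.
3. **Arm 2 versus arm 3 as a separate reference comparison**, not conditional on the arm 1 result. The Design section uses it to judge assay sensitivity, which matters most when arm 1 fails.
4. **Baseline means constrained equal across the randomised arms**, or baseline days as a covariate, in place of a free baseline difference. Drop the baseline significance test.

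This costs wording, one simulation rerun and modest model work. The downside is that a result at the non-primary follow-up alone is supportive only.

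If success at either follow-up is really wanted, 2.5% per test keeps the error at 3.6-4.9%. A test with 80% power at 5% then falls to 71%, and restoring 80% needs about 210 × 1.211 ≈ 255 per arm, or 765 in total. Naming one test avoids that, provided its restated power is adequate.

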### Data analyses

Data will be analyzed according to the ITT principle. Multiple imputation procedures, using the R package *mice* [87], will be used to address missing data. *mice* involves specifying a multivariate distribution for the missing data and drawing imputations from their conditional distributions by Markov chain Monte Carlo (MCMC) techniques. We intend to use 20 imputed data sets, as this has been deemed sufficient [87]. The imputation model will include all primary and secondary outcomes (see above). Adjunct variables, like sociodemographic data, will be included if they improve convergence within the imputation model.

Differences in primary and secondary continuous outcome variables between the two active study arms (1 and 2) at baseline and at both follow-up points will be tested using linear mixed models (LMM). The LMMs will be specified to model clusters and repeated measures by defining random effects for study condition and time (repeated measures). Appropriate distributions for non-normal continuous outcomes will be specified (e.g., negative binomial, zero-inflated). In addition to the ITT analyses, per-protocol analyses will be performed.

To investigate the exploratory research question of whether study arm 1 (mindfulness-based self-help IMI) results in a similar reduction in days of cannabis use as study arm 2 (CBT-based self-help IMI), a confidence interval approach will be used for the ES of the difference between these two study arms, using a two-sided 0.05 level of significance [54]. The equivalence margin is a priori set at d = 0.20, corresponding to the smallest value that would constitute a relevant effect [88]. The upper bound of the 95% CI for the ES will be compared against the predefined equivalence margin of d = 0.20 and must be below the margin to show equivalence.

Additional exploratory regression analyses will be conducted to determine whether baseline variables predict the frequency or quantity of cannabis use, severity of dependence (SDS), reduced psychiatric symptoms (PHQ-9, GAD-7), perceived stress (PSS-10) and mindfulness (MAAS) at 3 and/or 6 months follow-up, treatment retention, and adherence. For these analyses, we will use linear, multinomial, or binary regression models, depending on the scale used for the outcome measure. Treatment retention and client satisfaction will be compared between study arms one and two by Pearson chi-square analysis at week 6 (intervention end).

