Despite the potential advantages of CANreduce 3.0, the following limitations must be taken into account. First, and based upon previous research (e.g. [17]), relatively large drop-out rates are expected. Furthermore, it is possible that adherence to IMI is generally limited, due to the distant nature of such interventions [90]. However, according to the supportive-accountability model, [18] it is assumed that these issues have been somewhat ameliorated in CANreduce 3.0, via the addition of both a female and male eCoach. Secondly, it must be acknowledged that many contents in the modules offered in study arms 1 and 2 are provided in written form. Hence, a certain level of literacy is required. Thirdly, all measurements will be self-reported; and, though most of the measurements used have been validated in other clinical and research settings, they have not yet been validated as online assessments. On the other hand, participants in studies assessing previous versions of CANreduce also filled out questionnaires online, which did not seem to cause any (validity) issues.

In conclusion, we believe that version 3.0 of CANreduce will further our understanding of the effectiveness of IMI and MBI (and their combination) for the treatment of frequent cannabis users and will – if found effective – help to reach and support frequent cannabis users who might otherwise forgo care.

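### Twenty imputations are called sufficient without reference to the large drop-out expected; 100 would make the standard error and a borderline p-value less dependent on the seed, for computing time only

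*Protocol article*

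**What the plan says.** The Data analyses section of the protocol article follows the intention-to-treat principle and states that multiple imputation with the R package mice "will be used to address missing data". The imputation model contains all primary and secondary outcomes, with sociodemographic variables added if they help convergence. On the number of imputations it says: "We intend to use 20 imputed data sets, as this has been deemed sufficient". The only support is a citation.

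The Discussion names as its first limitation that "relatively large drop-out rates are expected". It gives no percentage, and neither section connects the number of imputations to the amount of missing data.

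The primary outcome is the number of days of cannabis use in the preceding 30 days, collected at baseline, six weeks, three months and six months (Table 3).

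**The concern.** Whether a given number of imputations is sufficient depends on how much information is missing. Relative efficiency, which describes the variance of the point estimate, is already close to 1 with few imputations. The standard error and degrees of freedom converge more slowly, because they rest on a between-imputation variance estimated from only m values, here 20. If much information is missing, that variance makes up much of the total, and its noise passes into the standard error, the interval and the p-value.

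At stake is reproducibility. Two analysts with the same data, model and code but different seeds could fall on opposite sides of 0.05 when the result is close. There is also a small, avoidable loss of power.

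**Working it through.** **The plan's own figures.** The number 20 has no derivation to reproduce. The stated power (above 80% with 210 per arm) can be neither confirmed nor refuted. The Power analysis section gives "The CANreduce 2.0 model estimate yielded an effect of b = -0.069" with p = 0.07, so |z| = 1.81 and the standard error is 0.069/1.81 = 0.0381. The effect was then lowered: "This value was reduced to -0.06 for the power analyses". Power of 80% at two-sided 0.05 needs a standard error of 0.06/(1.960 + 0.842) = 0.0214. Scaling by the square root of n, 210 per arm reaches this if the earlier estimate rested on about 210 × (0.0214/0.0381)² ≈ 66 or fewer per arm. That number is not in the article. Below, 80% therefore serves only as a nominal starting point.

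**Inputs.**
- m = 20, from Data analyses.
- 210 per arm, from Power analysis.
- Two-sided 0.05, which the article states only for the exploratory confidence interval and which I assume for the primary test.
- FMI from 0.2 to 0.7, which is my assumption because no rate is given.

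**Formulas.**
- Relative efficiency of the estimate: 1/(1 + FMI/m).
- Seed-to-seed coefficient of variation (CV) of the standard error. The between-imputation variance has a CV of √(2/(m − 1)), makes up a share FMI of the total variance, and the square root halves the effect. This gives FMI/√(2(m − 1)).
- Degrees of freedom: (m − 1)/FMI².
- Power: noncentral t with noncentrality 2.80/√(1 + FMI/m).
- Seed dependence of a p-value: simulation with the data held fixed and only the seed varied. The pooled estimate varies with variance FMI/m and the between-imputation variance as a scaled chi-square on m − 1. The test uses Barnard-Rubin degrees of freedom with 2 × 210 − 2 = 418 complete-data degrees of freedom. The starting point is a result with p = 0.03 under infinitely many imputations.

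**Example at FMI 0.5, m = 20.** Relative efficiency is 1/(1 + 0.025) = 0.976. The CV of the standard error is 0.5/√38 = 8.1% (8.2% by simulation). Degrees of freedom are 19/0.25 = 76. The noncentrality is 2.80/√1.025 = 2.77, giving power of 78.0%.

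| FMI | m | CV of SE | df | Share of seeds with p ≥ 0.05 | Power |
|---|---|---|---|---|---|
| 0.2 | 20 | 3% | 475 | 6% | 79.4% |
| 0.3 | 20 | 5% | 211 | 14% | 79.1% |
| 0.5 | 20 | 8% | 76 | 26% | 78.0% |
| 0.7 | 20 | 11% | 39 | 36% | 76.6% |
| 0.2 | 100 | 1.4% | 2475 | about 0% | 79.9% |
| 0.3 | 100 | 2.1% | 1100 | 0.3% | 79.8% |
| 0.5 | 100 | 3.6% | 396 | 3% | 79.6% |
| 0.7 | 100 | 5.0% | 202 | 10% | 79.3% |

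The 95% seed range of the p-value that starts at 0.03, with m = 20, is 0.017 to 0.056 at FMI 0.2, 0.014 to 0.068 at 0.3, and 0.010 to 0.093 at 0.5. With m = 100 at FMI 0.5 it narrows to 0.019 to 0.051. A small part of the non-significant share comes from the lower degrees of freedom rather than from the seed.

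Across all trials with nominal 80% power, not only borderline ones, two seeds disagree about p < 0.05 in 5.2% of trials at FMI 0.3 and 7.9% at 0.5 with m = 20. With m = 100 the figure at 0.5 is 3.3%.

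**Imputations needed.** Setting FMI/√(2(m − 1)) = 0.05 gives m = 1 + 0.5 × (FMI/0.05)². That is 9 at FMI 0.2, 19 at 0.3, 51 at 0.5 and 99 at 0.7. Conversely, m = 20 meets the target up to FMI = 0.05 × √38 = 0.31.

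**The case against.** The strongest reply is that nothing here is invalid. Rubin's rules allow for a finite number of imputations through the degrees of freedom: at FMI 0.5 the critical value is 1.99 rather than 1.96. The estimate is unbiased by the choice of m, and relative efficiency is 0.976. All of this stands. A reader might infer that 20 imputations make the primary analysis wrong; the documents and the arithmetic do not support that.

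Second, the size rests on a quantity that the article does not give. A reader might take large drop-out to mean that half or more of the information is missing. That does not follow. The imputation model includes all outcomes, and cannabis use is measured at four time points alongside correlated scales, so FMI may lie below the drop-out rate. At FMI 0.2 to 0.3 the number 20 meets a 5% target, and that target is itself my choice.

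Third, the losses are modest. About 2 points of power at FMI 0.5 compare with a Monte Carlo standard error of √(0.8 × 0.2/1000) = 1.3 points in the plan's own 1000-run simulation, and the plan claims more than 80%. Some seed dependence remains with any finite m. The same noise enters the comparison with the d = 0.20 margin, but the article calls that analysis exploratory and I do not rest the point on it.

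Fourth, seeds and Monte Carlo error checks commonly belong in an analysis plan or code, so their absence here is no defect, and the wording states an intention. This also stands. What remains is that the article itself names a number, calls it sufficient, and does not relate that to the drop-out it expects.

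**Conclusion.** The point holds as a minor, free improvement. Whether 20 imputations suffice depends on an FMI that the article neither gives nor bounds. By a 5% limit on seed variation of the standard error they suffice up to about FMI 0.3. Beyond that, the variation reaches 8% at 0.5 and 11% at 0.7, and a result that would have p = 0.03 with unlimited imputations turns non-significant in about a quarter to a third of seeds. The power cost runs from under 1 point at FMI 0.2 to 3.4 points at 0.7. With 100 imputations the variation is at most 5.0% and power at least 79.3% over the whole range.

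These figures assume FMI between 0.2 and 0.7, a two-sided 0.05 primary test and 210 per arm. They do not show bias, a failure of Rubin's rules, or that the stated power is wrong.

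**What to change.** In Data analyses, replace the 20 imputed data sets with 100. Alternatively, state a rule: set m from the observed FMI of the primary contrast so that the CV of its standard error is at most 5%, roughly m = 1 + 0.5 × (FMI/0.05)². The fixed number is simpler and covers FMI up to 0.7, where the rule gives 99. Recording the seed in advance is sensible if the analysis plan does not already do so.

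The cost is computing time only. With 630 participants, 100 imputations are a small task, and the estimand, sample size and visit schedule do not change.

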**Methods:**

This paper details the protocol for a three-arm randomized controlled trial comparing a mindfulness-based self-help IMI (arm 1) and cognitive-behavioral therapy (CBT)-based self-help IMI (arm 2) versus being on a waiting list (arm 3) in their effectiveness reducing cannabis use in frequent cannabis users. Predictors of retention, adherence and treatment outcomes will be identified and similarities between the two active intervention arms explored. Both active interventions last six weeks and consist of eight modules designed to reduce cannabis use and common mental health symptoms. With a targeted sample size of *n* = 210 per treatment arm, data will be collected at baseline immediately before program use is initiated; at six weeks, immediately after program completion; and at three and six months post baseline assessment to assess the retention of any gains achieved during treatment.

The primary outcome will be number of days of cannabis use over the preceding 30 days. Secondary outcomes will include further measures of cannabis use and use of other substances, changes in mental health symptoms and mindfulness, client satisfaction, intervention retention and adherence, and adverse effects. Data analysis will follow ITT principles and primarily employ (generalized) linear mixed models.

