#### Assessments, compensation, and randomization

Once they complete a baseline questionnaire (t0), participants will be randomly allocated by a random number generated by the server to one of three study arms. The masking technique will be partially single-blinded: participants will know if they were assigned to the waiting list control group or to one of the two intervention groups. However, in the latter case, they will be unaware of the particular intervention that they are receiving. The risk of disappointing participants who fail to receive their preferred intervention is essentially eliminated by describing both interventions as ‘an optimized version of a previous program’ without providing further details. Those participants who are assigned to study arms 1 or 2 can then immediately commence with the program, whereas controls assigned to study arm 3 will be informed that they must wait for six months to access the intervention. Besides the baseline questionnaire (t0), participants in all study arms will be asked to fill out an online assessment at six weeks (i.e., for study arms 1 and 2: immediately after they conclude the program; t1), three months (t2) and 6 months (t3) after their baseline assessment. Participants will earn 20 Swiss Francs for completing the 3-month follow-up assessment (t2) and 30 Swiss Francs for completing the 6-month follow-up assessment (t3). They can individually decide whether they wish to receive the total amount as an online voucher or to donate it to a charity. The study personnel is not blinded.

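### Baseline variables that are not outcomes enter the imputation model only if they help convergence; any left out would be attenuated in predictor regressions run on imputed follow-up outcomes

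*Protocol article*

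**What the plan says.** All references are to the protocol article.

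- **Missing data (Data analyses).** Multiple imputation by *mice*, with 20 data sets, "will be used to address missing data". The statement is general and is not tied to one model.
- **Contents of the imputation model (Data analyses).** All primary and secondary outcomes go in. For anything else: "Adjunct variables, like sociodemographic data, will be included if they improve convergence within the imputation model".
- **What counts as a secondary outcome (Measures, text after Table 3).** Quantity and frequency of use over seven days, "scores for the SDS, AUDIT-C, NIDA-ASSIST, PSS-10, PHQ-9, GAD-7, MAAS, and CSQ-I", and negative effects. CUDIT-R, DAST-10, ASRS, CHIME, meditation experience, years of use and sociodemographics are not on this list, so they fall under the convergence rule.
- **Predictor analyses (Data analyses).** "Additional exploratory regression analyses will be conducted to determine whether baseline variables predict the frequency or quantity of cannabis use", and likewise SDS, PHQ-9, GAD-7, PSS-10 and MAAS at 3 and/or 6 months, retention and adherence. The abstract states the aim: "Predictors of retention, adherence and treatment outcomes will be identified".
- **Drop-out (Discussion).** "relatively large drop-out rates are expected", without a figure.
- **Timing (Assessments, compensation, and randomization).** "Once they complete a baseline questionnaire (t0), participants will be randomly allocated by a random number generated by the server". Baseline variables should therefore be essentially complete.

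**The concern.** Convergence describes how the sampler behaves. It does not show whether the imputation model is compatible with the analysis that follows. A variable belongs in the model because a later analysis uses it, or because it predicts the outcome or drop-out. Adding variables seldom improves convergence, so the rule gives little reason to admit the variables that need to be there.

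If a predictor is absent from the imputation model, the imputed follow-up values relate to it only through the variables that are present. A regression on the completed data then mixes observed records, which carry the true relation, with imputed records, which carry less or none of it. The coefficient shrinks.

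At stake is the reading of the predictor results. A null result for, say, a sociodemographic variable could not be told apart from an imputation artefact. Predictors inside the model, such as baseline PHQ-9, would not be shrunk in this way, so the two groups could not be compared fairly.

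**Working it through.** The plan gives no figure for this point. Its only power figure concerns arm 1 against arm 3 and plays no part here.

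**Inputs from the article:** n = 630 in total, 420 in the two active arms; 20 imputations; the entry rule above.
**Assumed, because the article is silent:** missing fraction m, predictor slope β, correlations, normal outcomes, and the form of the regression.

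**Step 1. Expected shrinkage.** Take outcome Y, its baseline Y0 and predictor X, all standardised, with Y = βX + 0.5·Y0 + error. X is omitted from the imputation model and data are missing completely at random.

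- *Regression adjusted for Y0.* Imputed records carry no slope on X given Y0, so the retained fraction is 1 − m: 0.80, 0.60 and 0.40 at m = 0.2, 0.4 and 0.6.
- *Adjusted, with other included outcomes explaining a share R² of X.* The retained fraction is 1 − m(1 − R²). At m = 0.4: R² = 0.25 gives 1 − 0.4 × 0.75 = 0.70; R² = 0.50 gives 0.80.
- *Unadjusted, X correlated ρ with Y0.* The true slope is β + 0.5ρ and the imputed records carry (0.5 + βρ)ρ. With β = 0.15 and ρ = 0.3 these are 0.30 and 0.545 × 0.3 = 0.1635, a ratio of 0.545. At m = 0.4 the retained fraction is 0.6 + 0.4 × 0.545 = 0.82.

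**Step 2. Simulation of the simple case** (β = 0.15, 20 imputations, Rubin's rules, 300 replicates per cell). Retained fraction of the slope, over n = 420 and 630:

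| Missing | Adjusted, X omitted | Unadjusted, ρ = 0.3, X omitted |
|---|---|---|
| 20% | 0.80–0.81 | 0.90–0.91 |
| 40% | 0.58–0.60 | 0.82 |
| 60% | 0.39–0.40 | 0.72–0.73 |

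With X included, the fraction is 0.95–1.02 in every cell. Leaving out the adjustment does not help by itself: with ρ = 0, the unadjusted slope at 40% missing is still only 0.59–0.61 of the truth.

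**Step 3. Simulation with intermediate waves** (n = 630, slope 0.20, missing at random, one secondary outcome in the model, early or late drop-out, X correlated 0 or 0.5 with that outcome). With X omitted, the adjusted slope keeps 73–84%, 65–79% and 56–77% at 30%, 40% and 50% missing. At 40% the unadjusted slope keeps 78–87%. With X included, recovery is 99–100%.

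**Step 4. Power** (Step 2 model, adjusted, ρ = 0; omitted against included):

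| Missing | n = 630 | n = 420 |
|---|---|---|
| 20% | 0.94 vs 0.99 | 0.79 vs 0.92 |
| 40% | 0.66 vs 0.90 | 0.41 vs 0.80 |
| 60% | 0.13 vs 0.76 | 0.03 vs 0.59 |

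With a larger slope of 0.20, n = 630 and 40% missing, power with X omitted is 0.92, 0.96 or 0.98 when the included outcomes explain 0, 25% or 50% of X, against 0.99 or more with X included. In the unadjusted case with ρ = 0.3, power is hardly changed at any drop-out level.

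**The case against.** Several objections stand and limit the point.

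- **Data set.** The predictor paragraph does not say that these regressions use the imputed data. If they use observed outcomes, this bias does not arise. The general missing-data statement points to imputed data but does not settle it.
- **Conditional exclusion.** A reader might infer that the non-outcome baseline variables are kept out of the model. The text makes exclusion possible, not certain.
- **Unnamed predictors.** The article speaks only of baseline variables. Which of the scales outside the outcome list will be tested is an inference.
- **Reach.** A reader might infer that every predictor coefficient is biased. Retention and adherence come from diary and module-page records, not follow-up questionnaires, so regressions on them escape. Baseline scores of outcome scales are in the model on the natural reading of the outcome rule.
- **Missed predictors.** A reader might infer that real predictors will be missed. Step 4 does not support this as a general statement: the loss is about 5 points at 20% missing with n = 630, and small for a slope of 0.20 even at 40%.
- **Thin simulated model.** The plan's model holds many outcomes, most measured repeatedly, and some overlap in content with the scales at issue (MAAS with CHIME, NIDA-ASSIST with DAST-10). More overlap means less shrinkage.

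One objection does not stand: that the list of imputation variables is ordinary analysis-plan detail. The article states an entry rule, and that rule uses the wrong criterion.

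**Conclusion.** The concern holds in conditional form. If the predictor regressions of 3- and 6-month outcomes use the imputed data, the coefficient of any tested variable that the convergence rule leaves out is biased toward zero. At an assumed 40% missing, the baseline-adjusted slope is roughly 0.6 to 0.8 of its true value, and about 1.0 when the variable is included. Shrinkage is milder where the variable correlates with outcomes in the model, and in an unadjusted regression where it correlates with the outcome's own baseline. Power loss ranges from negligible to large.

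These sizes rest on assumed drop-out, slopes, correlations and normal outcomes. The direction does not depend on the particular values chosen. The arm comparisons are not touched by this point, and none of the three hypotheses concerns predictors. Since the analyses are labelled exploratory, the priority is modest. Predictor identification is nevertheless a stated aim, and the repair is cheap.

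**What to change.** Replace the sentence on adjunct variables with:

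> *All baseline variables tested in the predictor regressions are included in the imputation model regardless of convergence; further variables are included if they predict the outcomes or drop-out.*

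Name the candidate predictors and state which data set the predictor regressions use. If the enlarged model becomes unstable, run those regressions on observed outcomes instead. In the simple simulation with data missing completely at random, this recovered 0.97 to 1.02 of the true slope. It would be less safe if drop-out depends on variables outside the regression.

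The cost is one sentence and a few lines of code. The variables are collected before randomisation, so they add little missing data of their own. The downside is a somewhat larger imputation model.
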